### Sample size calculation

The design of this study is novel. According to the trial design and previous literature assessment, the sample size will be calculated based on hypothetical changes in MoCA score (28) or UPDRS motor score (10) at week 12. With a power of 90% and an alpha of 5% (two-sided). The SD from our feasibility study is used and our power calculation considered our planned analysis method, by means of an analysis of covariance (ANCOVA) in which baseline measurements served as a covariates, reducing the needed sample size (29). we calculated the minimum sample size (effect size = 0.3) in MoCA score (SD = 2.07, Difference = 1.8) to be 28 participants per group and UPDRS motor score (SD = 2.55, Difference = 1.9) to be 38 through PASS software (version 15.0.5). Therefore, With a 15% dropout rate considered, a total sample size of 135 participants will be necessary.

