### Follow-up

After 12 weeks of treatment, participants will undergo a 1-month follow-up period. As they will not have access to equipment and professionals during this period, we will not require them to continue with the corresponding treatment but instead encourage them to resume their daily routine. After the 1-month follow-up, all participants will be required to return to the hospital to reassess of the results.

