### Statistical analysis

All primary and secondary analyses will be conducted on an intention-to-treat (ITT) basis. Modified ITT analysis included all randomized participants who completed at least 8 weeks of the intervention. Primary analyses will be conducted using multiple imputation methods for missing observations at baseline, post intervention, and at follow-up, assuming missing data are missing at random. Prespecified sensitivity analyses will be conducted for all participants using complete-case data at each time point.

Continuous data will be presented as mean ± SD or median ± quartile interval, while enumeration data will be presented as numbers and percentages. Between-group differences in demographic and baseline variables, as well as assessment variables, will be assessed using a chi-square test or the Fisher exact test for categorical variables and a one-way analysis of variance (ANOVA) or the Kruskal-Wallis test for continuous variables as appropriate. Intervention effects on primary and secondary continuous outcome measures will be compared by means of mixed repeated-measures analysis of variance, with and without adjustment for baseline and time-varying covariates (e.g., age, sex, and Hoehn and Yahr stage). Pairwise comparisons between the Yijinjing group and the two other groups will be conducted only if the omnibus F-test statistics indicated that the null hypothesis should be rejected. The primary analysis will to determine whether Yijinjing training improved the MoCA and UPDRS-III score compared with brisk walking training and control at 12 weeks. These continuous outcomes will be assessed by the 1-way analysis of variance model at 12 and 16 weeks. All statistical analyses will be conducted using SPSS software, version 24 (IBM). *p* value < 0.05 will be considered statistically significant. An independent statistician will carry out all statistical analyses.

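### The omnibus F that must reject before any Yijinjing comparison is not tied to the 12-week baseline-adjusted ANCOVA, and the sample size makes no allowance for it

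*Protocol article*

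**What the plan says.** All of this is in the protocol article.

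- **Model.** Statistical analysis: "Intervention effects on primary and secondary continuous outcome measures will be compared by means of mixed repeated-measures analysis of variance". Both adjusted and unadjusted versions are foreseen. Outcomes are measured at baseline, 12 weeks and one month after treatment ends.
- **Gate.** The next sentence reads "Pairwise comparisons between the Yijinjing group and the two other groups will be conducted only if the omnibus F-test statistics indicated" rejection of the null. It does not name the model, the effect (group or group-by-time) or the visit.
- **Primary question.** The section then asks whether Yijinjing "improved the MoCA and UPDRS-III score compared with brisk walking training and control at 12 weeks". It goes on to assign these outcomes a one-way ANOVA at 12 and at 16 weeks.
- **Power.** Sample size calculation: "With a power of 90% and an alpha of 5% (two-sided"), for a week-12 difference analysed "by means of an analysis of covariance (ANCOVA) in which baseline measurements served as a covariates". The cognitive outcome enters as "in MoCA score (SD = 2.07, Difference = 1.8) to be 28 participants per group". For the motor outcome, the corresponding inputs and result are given as "UPDRS motor score (SD = 2.55, Difference = 1.9) to be 38 through PASS software".
- **After week 12.** Follow-up: "we will not require them to continue with the corresponding treatment".

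**The concern.** The primary question is two contrasts at one visit. Permission to test them comes from an omnibus F that, read in order, belongs to a model over three visits. A group main effect in that model averages the 12-week difference with baseline, where randomisation leaves no expected difference, and with follow-up, when training has stopped. A group-by-time F has 4 degrees of freedom, part of them spent on follow-up. Any three-arm F also spends information on walking versus control, which is not part of the primary question.

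A real 12-week benefit of the assumed size could therefore go untested because a different hypothesis was not rejected. A gate can only keep or lower the power of the contrast behind it, and UPDRS-III, which sets the sample size, has no reserve.

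**Working it through.** **1. Reproduce the plan's sample size.** With n = 2(z₀.₉₇₅ + z₀.₉₀)²(SD/Δ)² and (1.960 + 1.2816)² = 10.507:

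- MoCA: 21.015 × (2.07/1.8)² = 27.8, so 28 per group.
- UPDRS-III: 21.015 × (2.55/1.9)² = 37.9, so 38 per group.
- Dropout: 38/0.85 = 44.7, so 45 per arm and 3 × 45 = 135.

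All three match. The plan is powered as an ungated two-arm comparison at one visit. Exact t-test power for UPDRS-III at 38 per arm is 0.89. For MoCA at 38 per arm it is 0.96.

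**2. Gate on the unadjusted 12-week one-way F.** λ = n Σ(μᵢ − μ̄)²/SD², with 2 and 111 degrees of freedom, UPDRS-III, 38 per arm.

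- Walking equal to control: Σ = 1.9² × 2/3 = 2.407, λ = 38 × 2.407/6.5025 = 14.06, and the gate passes with probability 0.92.
- Walking midway: Σ = 2 × 0.95² = 1.805, λ = 10.55, and it passes with probability 0.83.

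**3. Gate on the group main effect over three visits.** If a share p of the effect remains at follow-up, the mean difference is 1.9(1 + p)/3 and the between-patient variance is SD²(1 + 2ρ)/3. Take ρ = 0.5 and walking equal to control:

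- p = 1: difference 1.267, variance 4.335, λ = 38 × (1.267² × 2/3)/4.335 = 9.4. The gate passes about 0.77 of the time.
- p = 0.5: difference 0.95, λ = 5.3. The gate passes about 0.52 of the time.

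**4. Joint power by simulation.** This is the probability that the gate passes and Yijinjing versus control is significant at 12 weeks. The runs use UPDRS-III, 38 per arm, compound symmetry and several thousand trials per cell, so simulation error is about 0.01. The documents do not give the correlation (0.5 here), the persistence at follow-up or the walking effect; these are assumptions. SD 2.55 is read as the SD of the score.

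| Gate | Walking = control, effect kept | Walking = control, half kept | Walking midway, effect kept | Walking midway, half kept |
|---|---|---|---|---|
| Group main effect | 0.75 | 0.50 | 0.63 | 0.40 |
| Group-by-time | 0.85 | 0.79 | 0.79 | 0.68 |
| Unadjusted 12-week F | 0.87 | 0.87 | 0.82 | 0.82 |
| 12-week ANCOVA F, then ANCOVA contrast | 0.95 | 0.95 | 0.92 | 0.91 |
| No gate, ANCOVA with Holm | 0.95 | 0.95 | 0.93 | 0.92 |

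**5. Sensitivity.**

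- At correlation 0.7 the group-by-time gate gives about 0.85 to 0.90, so little or nothing is lost.
- At correlation 0.3 the ANCOVA F gate gives about 0.85 to 0.90.
- If 2.55 is already net of baseline, the ANCOVA F gate has roughly the power of the unadjusted 12-week row, 0.82 to 0.88.
- MoCA at 38 per arm and correlation 0.5, over the same four scenarios: about 0.92 to 0.96 with the unadjusted 12-week F, 0.84 to 0.95 with group-by-time, and 0.52 to 0.88 with the group main effect.

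**The case against.** The strongest reply is that the text never says the gate is the repeated-measures F. The sentences after it fix the question at 12 weeks and name a one-way ANOVA there. That ANOVA's F is also an omnibus test, and it concerns the same means as the contrasts. On that reading, gating in three arms is a recognised way to control the familywise error. This stands: the repeated-measures reading is the natural one from the order of the sentences, but not the only one.

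It is also fair that the lowest figures need several things together: an unadjusted group main effect, baseline counted as an outcome visit, and assumed values for correlation, persistence and walking. For a randomised pre/post design, many would take group-by-time as the relevant F. The section also allows adjustment for baseline. In a simulation at correlation 0.5, a baseline-adjusted group effect averaged over 12 and 16 weeks gave joint power of 0.86 to 0.96.

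A reader might infer that 90% power is lost under every reading. The figures do not support that. Group-by-time at high correlation stays near 0.90, a 12-week ANCOVA gate exceeds 0.90 at correlation 0.5, and MoCA often keeps more than 0.90. A reader might also infer that the gate itself must go. Like for like, an ANCOVA F gate and ANCOVA with Holm differ by 0 to 2 points, so most of the gain over the unadjusted procedures comes from baseline adjustment.

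A condensed article may leave detail to an analysis plan. Here, though, it states an explicit condition for making the primary comparisons, and places it beside models that differ from the one used for power.

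**Conclusion.** The point holds in this form. The gating rule, as placed, reads as the repeated-measures F. The alternative in the text is an unadjusted 12-week F. Neither is the ANCOVA on which the power statement rests, and the sample size includes no gate. For UPDRS-III at 38 evaluable per arm, joint power falls from about 0.89 to 0.90 ungated to 0.40 to 0.75 (group main effect), 0.68 to 0.85 (group-by-time, up to about 0.90 at correlation 0.7) or 0.82 to 0.88 (unadjusted 12-week F). These sizes rest on an assumed correlation of 0.5, persistence of 100% or 50%, and a walking effect of zero or half. The text does not establish which F is meant, so the size of the loss is conditional. The mismatch between gate, primary question and power calculation is not.

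**What to change.** 1. For MoCA and UPDRS-III, name the two 12-week contrasts (Yijinjing versus control, Yijinjing versus brisk walking) from the baseline-adjusted ANCOVA of the Sample size calculation as the primary tests.
2. If an omnibus gate is kept, define it as the 12-week group F of that same ANCOVA. Otherwise replace it with Holm across the two contrasts. Either is acceptable.
3. Keep the repeated-measures model as a secondary description of the time course, with no control over the primary tests.
4. Restate the power for the procedure actually used. Say whether the SDs of 2.07 and 2.55 are before or after baseline adjustment, and state the assumed walking effect.

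The cost is a change of wording, and possibly a slightly lower stated power. Data collection does not change.

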#### Primary outcome

Cognitive and motor functions will be measured using the MoCA and UPDRS assessments, respectively. The MoCA evaluates 8 aspects of the cognitive domain, including visual space and execution, naming, memory, attention, language, abstraction, delayed recall, and orientation (33). With a total score is 30, a score of ≥26 indicates no cognitive impairment. Alternate Chinese versions 7.1 and 7.2 will be used to minimize the learning effect before and after the treatment. On the other hand, the UPDRS is the most widely used, well validated clinical rating scale for PD, UPDRS-III is the motor section of UPDRS, through 18 tasks, each scored from 0 to 4, with a maximum score of 72 (34).

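### Two primary outcomes are each tested at 0.05 with no success rule: if either may carry the claim the error is about 8-10%, and if both must succeed the stated 90% power is not the joint power

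*Protocol article*

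**What the plan says.** The Primary outcome section names two scales: "Cognitive and motor functions will be measured using the MoCA and UPDRS assessments, respectively". No order or priority is given.

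The Sample size calculation section works "based on hypothetical changes in MoCA score (28) or UPDRS motor score (10) at week 12", at two-sided 5% and 90% power. It gives "in MoCA score (SD = 2.07, Difference = 1.8) to be 28 participants per group", and 38 per group for UPDRS-III (SD 2.55, difference 1.9). The larger figure is carried to a total of 135 after 15% dropout.

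The Statistical analysis section sets the primary question as "whether Yijinjing training improved the MoCA and UPDRS-III score compared with brisk walking training and control at 12 weeks". It has one gate: "Pairwise comparisons between the Yijinjing group and the two other groups will be conducted only if the omnibus F-test statistics indicated" rejection of the null hypothesis. It closes with one threshold for all tests: a p "value < 0.05 will be considered statistically significant". The same continuous outcomes are also assessed at 16 weeks.

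The article contains no split of alpha between the outcomes, no testing order, and no statement of what makes the trial positive.

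**The concern.** With two primary outcomes, the rule for combining them decides both the error rate and the power of the headline conclusion. The F gate does not supply that rule. It limits false claims among three arms for one outcome, and each outcome then gets its own gate at a full 5%.

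Two rules are open. If success on either outcome is enough, there are two chances to be wrong and the overall level exceeds 5%. If both must succeed, the level is safe, but the power of the joint event is not the 90% computed for a single comparison. Because neither rule is written down, a trial that succeeds on one outcome only could be called positive or negative once the results are known. Later analysis cannot undo that.

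**Working it through.** **Inputs.** From the Sample size calculation section: alpha 0.05 two-sided, power 90%, MoCA difference 1.8 with SD 2.07, UPDRS-III difference 1.9 with SD 2.55, dropout 15%. The correlation between the outcomes is not given, so 0 to 0.8 is assumed.

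**1. Reproduce the plan's figures.** For one pairwise comparison, n per group = 2(1.960 + 1.282)² (SD/difference)², which is 21.01 × (SD/difference)².
- MoCA: 21.01 × (2.07/1.8)² = 27.8, so 28.
- UPDRS-III: 21.01 × (2.55/1.9)² = 37.9, so 38.
- Total: 38/0.85 = 44.7, so 45 per arm and 135 overall.

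All three match. The 90% is therefore the power of one pairwise comparison on one outcome, with no further reduction of the quoted SD for baseline adjustment.

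**2. Either outcome suffices: false-positive rate at week 12.** With independent outcomes, 1 − 0.95² = 9.75%. Positive correlation lowers this to 9.1% at 0.5 and 7.8% at 0.8. The article's procedure (one-way F-test, then pairwise t-tests at 0.05) was simulated with no true differences and 38 per arm:

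| Outcome correlation | Any F-test rejects | Any gated Yijinjing comparison significant |
|---|---|---|
| 0 | 9.9% | 8.2% |
| 0.5 | 8.9% | 7.4% |
| 0.8 | 7.9% | 6.7% |

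The right-hand column is lower because a rejecting F-test may reflect only the contrast between brisk walking and control.

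**3. Both outcomes must succeed: power at 38 evaluable per arm.** Single-comparison power, by normal approximation, is Φ(difference/(SD√(2/38)) − 1.96).
- MoCA: Φ(3.790 − 1.960) = 96.6%.
- UPDRS-III: Φ(3.248 − 1.960) = 90.1%.
- Both outcomes against one comparator, independent: 0.966 × 0.901 = 87.1%.

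The table adds the case where both comparators must also be beaten. It assumes the full planned difference against each, and the comparisons share the Yijinjing arm.

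| Outcome correlation | One comparator, normal approximation | One comparator, F gate and t-tests | Both comparators, normal approximation | Both comparators, F gate and t-tests |
|---|---|---|---|---|
| 0 | 87.1% | 83% | 78.4% | 77% |
| 0.5 | 88.2% | 85% | 80.3% | 79% |
| 0.8 | 89.3% | 86% | 82.2% | 80% |

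The ranges are therefore about 83-89% against one comparator and 77-82% against both.

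**4. Sensitivity to baseline adjustment.** If the quoted SDs are unadjusted and ANCOVA reduces them by √(1 − ρ²), where ρ is the correlation of baseline with follow-up, simulated power for all four comparisons rises from about 77-79% at ρ = 0 to about 91% at ρ = 0.5 and 99% at ρ = 0.7. The article gives no ρ.

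**5. Cost of Holm.** Two-arm t-test power for UPDRS-III at 38 per arm is 89.4% at alpha 0.05 and 82.9% at 0.025.

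**The case against.** The best reply has four parts.

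- **No real conflict between the sections.** A reader might infer that the sample size section lets either outcome win while the analysis section demands both. The text does not support that. The first may only describe two separate calculations, of which the larger is kept, and the second may only list what is tested. This stands: the defect is a missing rule, not two rules in conflict.
- **The power loss can be overstated.** It is tempting to say that requiring both outcomes cuts power to 78%. That figure needs both outcomes and both comparators. Against one comparator the loss is small, because MoCA alone has about 97% power at 38 per arm. The article does not say which comparator its planned differences refer to, and with a useful baseline correlation the joint power could exceed 90%. This also stands, although 28 and 38 reproduce without any such gain.
- **Week 16 adds little.** A reader might count it as further inflation. Both sections place the primary question at 12 weeks, so the later visit needs only a label. The total of 96 in the Abstract, against 135, would lower power further, but that is a separate contradiction and carries no weight here.
- **Multiplicity detail often sits in an analysis plan that is not shown.** This has some force, but the article does set out a gate and an unqualified threshold. Followed as written, they do not hold 5% across the two outcomes.

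**Conclusion.** The point holds. Two primary outcomes are each tested at an unadjusted 0.05, the F gate works only within an outcome, and no success rule is stated.

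If either outcome can carry the claim, the week-12 error is about 8-10% or 7-8%, depending on whether any rejecting F-test or only a gated Yijinjing comparison counts. This rests on assumed outcome correlations of 0.8 to 0. If both must succeed, type I error is not a problem, but the 90% should not be quoted for that event. The joint power is about 83-89% or 77-82%, depending on whether one or both comparators must be beaten. These power figures assume 38 evaluable per arm, the planned differences against every comparator that counts, and no gain from ANCOVA.

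The rule has to be fixed before unblinding because it defines a positive trial.

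**What to change.** State one rule for week 12 in the Statistical analysis section, and match the Sample size calculation section to it.

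- **Either outcome may succeed.** Apply Holm across MoCA and UPDRS-III: the smaller p-value is tested at 0.025 and, if it passes, the other at 0.05. Keep the F gate within each outcome. The cost is a fall in first-step two-arm power for UPDRS-III at 38 per arm from about 89% to 83%.
- **Both outcomes must succeed.** Keep 0.05 for each, say whether both comparators must be beaten, and replace the 90% with the matching joint power. Give the assumed outcome correlation, the assumed difference against each comparator, and any baseline correlation relied on.

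Under either rule, label the 16-week tests as secondary. Both options are changes of wording and need no new data or visits. The sample size changes only if the sponsor wants 90% power for the rule chosen.

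### No single primary 12-week analysis is named: the sample size section plans ANCOVA on baseline, while the statistical section gives repeated-measures ANOVA with and without adjustment, and then one-way ANOVA

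*Protocol article*

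**What the plan says.** **Sample size calculation.** The power calculation is said to reflect the planned analysis, "by means of an analysis of covariance (ANCOVA) in which baseline measurements served as a covariates, reducing the needed sample size". The inputs are 90% power and two-sided alpha 5%. For cognition the result is "in MoCA score (SD = 2.07, Difference = 1.8) to be 28 participants per group". For the motor outcome, the corresponding entry reads "UPDRS motor score (SD = 2.55, Difference = 1.9) to be 38 through PASS software". On the source of the SDs the section says only "The SD from our feasibility study is used". It does not say whether they are raw SDs or SDs left after adjustment for baseline, and it gives no baseline-outcome correlation.

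**Statistical analysis.** Effects on primary and secondary continuous outcomes are to be "compared by means of mixed repeated-measures analysis of variance, with and without adjustment for baseline and time-varying covariates", with age, sex and Hoehn and Yahr stage as examples. Pairwise comparisons of Yijinjing with the other two arms follow only if an omnibus F-test rejects. The section then defines the primary question as MoCA and UPDRS-III at 12 weeks against both other arms, and continues: "These continuous outcomes will be assessed by the 1-way analysis of variance model at 12 and 16 weeks". That sentence names no covariate.

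**The concern.** Two sections of the same article describe the primary analysis differently, and the second offers more than one model. This is not a detail left to an unseen SAP: no SAP could agree with both sections as written.

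Two things are at stake. The first is that the confirmatory result is undefined. Each primary outcome has three candidate p-values in the Statistical analysis section (repeated-measures adjusted, repeated-measures unadjusted, one-way ANOVA) and a fourth if the ANCOVA of the sample size section is counted. There are two primary outcomes, and nothing stops the choice from being made after the results are seen. The gate shares the problem, because the omnibus F-test could come from any of these models.

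The second is precision. The model placed next to the primary question ignores the baseline score, although that score is collected and the sample size section says that it will be used.

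**Working it through.** **Step 1. The passages side by side**

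| Place | Model for the primary outcomes | Baseline score as covariate? |
|---|---|---|
| Sample size calculation | ANCOVA | Yes |
| Statistical analysis, general sentence on effects | Mixed repeated-measures ANOVA, two versions | Unclear: baseline covariates are mentioned, but the examples do not include the outcome's own baseline score |
| Statistical analysis, after the 12-week question | One-way ANOVA at 12 and 16 weeks | None named |

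No sentence ranks these models.

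**Step 2. Reproduce the stated sample size**

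Inputs from the sample size section: difference 1.8 and SD 2.07 (MoCA); difference 1.9 and SD 2.55 (UPDRS-III); two-sided alpha 0.05; power 0.90; 15% dropout.

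Unadjusted two-group formula, normal approximation: n per group = 2(1.960 + 1.282)² SD²/difference², with (1.960 + 1.282)² ≈ 10.507 before rounding.

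- MoCA: 2 × 10.507 × 2.07²/1.8² = 27.8, so 28. Stated: 28.
- UPDRS-III: 2 × 10.507 × 2.55²/1.9² = 37.9, so 38. Stated: 38.
- Dropout: 38/0.85 = 44.7, so 45 per arm, and 3 × 45 = 135. Stated: 135.

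All three figures reproduce with no covariate in the formula. An ANCOVA reduction would multiply n by (1 − ρ²). At ρ = 0.5 that gives 27.8 × 0.75 = 20.8, so 21, and 37.9 × 0.75 = 28.4, so 29. No such reduction is visible, unless the SDs entered were already residual SDs.

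**Step 3. What dropping the baseline score costs**

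For one follow-up score, the variance of the unadjusted comparison relative to ANCOVA is 1/(1 − ρ²), where ρ is the correlation between baseline and week 12. The article gives no ρ, so the values here are assumptions: ρ = 0.5 gives 1/0.75 = 1.33, and ρ = 0.7 gives 1/0.51 = 1.96.

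**Step 4. Pairwise power for UPDRS-III at 38 per group**

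Two-group t-test, difference 1.9, two-sided alpha 0.05. The noncentrality is (1.9/SD) × √(38/2).

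| What 2.55 is | ρ | SD, unadjusted | Power, unadjusted | SD, ANCOVA | Power, ANCOVA |
|---|---|---|---|---|---|
| Raw SD | 0.5 | 2.55 | 89% | 2.55 × √0.75 = 2.21 | 96% |
| Residual SD | 0.5 | 2.55/√0.75 = 2.94 | 79% | 2.55 | 89% |
| Residual SD | 0.7 | 2.55/√0.51 = 3.57 | 63% | 2.55 | 89% |

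The 89% falls just short of the planned 90% because the t-test replaces the normal approximation. MoCA at 28 per group behaves in nearly the same way: 89% unadjusted if 2.07 is raw; 79% (ρ = 0.5) or 63% (ρ = 0.7) if it is residual.

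These are pairwise figures, not the power of the three-arm omnibus F-test. With the stated SD taken as raw, that test has about 92% power at 38 per group if one arm differs from the other two, and about 83% if the third arm lies midway.

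**The case against.** **The sections can be read together.** The repeated-measures ANOVA could be the overall model and the one-way ANOVA the test at each visit. The adjusted repeated-measures version may also include the baseline score, so it would be too strong to say that the section never adjusts for it. Both points are fair. But that reading still leaves the 12-week comparison unadjusted, contrary to the sample size section, and still does not say which result is primary.

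**The trial may not lose its planned power.** This objection stands. A reader might infer that, because the article says it was sized for ANCOVA, a one-way ANOVA must be underpowered. The figures do not support that: 28 and 38 are the unadjusted numbers, and with raw SDs the unadjusted pairwise test keeps about 89%. The shortfall needs residual SDs, which the article does not state.

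**The one-way ANOVA is valid.** This also stands. A reader might take chance baseline imbalance to mean bias. Under randomisation the unadjusted comparison is unbiased and keeps its type I error rate; the argument for ANCOVA is one of precision.

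**The repeated-measures test may suit the question.** A reader might infer that its group effect averages in the baseline visit and so dilutes the 12-week effect. That would require baseline to be a level of time and the group main effect to be the test; the article says neither. Any figure for the dilution would also need an assumed correlation structure and an assumed effect at the follow-up visit. The point is not made here.

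**Conclusion.** The contradiction is real and must be resolved before unblinding. The article plans ANCOVA in one section, describes three other analyses of the same outcomes in another, ranks none of them, and attaches the gatekeeping F-test to none. This conclusion needs no assumption about ρ or the SDs.

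The cost in precision is conditional. Relative to ANCOVA, the one-way ANOVA inflates variance by 1.33 to 1.96 for ρ of 0.5 to 0.7, which is an assumed range. With raw SDs this is forgone efficiency (89% instead of 96% for UPDRS-III at ρ = 0.5), not a failure to reach the planned power. With residual SDs it is a true shortfall, to about 79% or 63%. The article does not allow a choice between the two cases. If the SDs are raw, the statement that ANCOVA reduced the sample size is not borne out by the figures.

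**What to change.** Reconcile the two sections as follows.

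- Name one primary analysis for each primary outcome: the week-12 score by ANCOVA on randomised group, with that outcome's baseline score as covariate.
- State that the omnibus F-test and the pairwise contrasts of Yijinjing with brisk walking and with control come from this model.
- Label the repeated-measures ANOVA and the one-way ANOVA as supportive.
- Use the same baseline-adjusted approach at week 16.
- In the sample size section, say whether 2.07 and 2.55 are raw or residual SDs. If they are raw, correct the claim that ANCOVA reduced the required number.

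Further covariates such as age, sex and Hoehn and Yahr stage are optional; this point does not depend on them.

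The cost is wording only. Baseline MoCA and UPDRS-III are already in the assessment schedule, and no visit, measurement or participant is added.
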